## I. Study Overview

### a. Study Aims and Objectives

#### **Primary Aim:**

To determine the change from baseline in minutes per day spent in moderate or vigorous physical activity (MVPA) as measured by accelerometry. We hypothesize that the *GoKids* intervention will more effectively increase time spent in MVPA compared to baseline vs. the *Advice-Only* condition.

#### **Secondary Aims:**

Cardiorespiratory fitness will improve in the group receiving the *GoKids* intervention more than in the group in the *Advice-Only* condition.

**Endpoint:** Cardiorespiratory fitness will be assessed in both groups pre- and post intervention using a modified FitnessGram test. FitnessGram tests will be supervised by [name], who will also interpret these data.

Anthropometric characteristics will improve in the group receiving the *GoKids* intervention more than in the group receiving *Advice-Only*.

**Endpoints:** Percent body fat by BIA, degree of obesity by BMI percentile, waist circumference, blood pressure. Drs. [name], [name] and [name] will interpret the anthropometric data.

Non-fasting total cholesterol (TC) and HDL will improve from baseline in the group receiving the *GoKids* intervention more than in the group receiving *Advice-Only*.

**Endpoint:** Change in Cholestech TC and HDL from baseline. Dr. [name] will evaluate and follow-up lipid parameters.

Psychosocial measures of physical activity and self-perception will be positively affected by participation in *GoKids* more than the *Advice-Only* condition, including physical activity self efficacy, physical activity social support, physical activity perceived barriers, physical activity enjoyment, competence and global self-worth.

**Endpoints:** Physical activity self efficacy, physical activity social support, physical activity perceived barriers, and physical activity enjoyment will be measured with scales that were validated for use in the TAAG study with 6th grade children (Dishman 2009). Competence and global self-worth will be measured with the modified Harter Self-Perception Profile Scale (Harter 1985). [name] will analyze and interpret these data.

Exer-gaming is a feasible way to increase moderate and vigorous physical activity in elementary aged children.

**Endpoints:** Successful recruitment of students, extent of implementation of intervention activities measured by student attendance/participation rates in intervention, student's level of enjoyment in or satisfaction with the intervention activities, retention rate in the study, costs to implement the intervention, barriers to and facilitators of implementation.

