Recently there has been increased interest in the use of interactive and new technologies to promote physical activity, prevent or reverse unhealthy weight, and improve physical fitness in youth ([name] 2007; An (in press); Daley 2009). These technologies include popular video games that feature player movement, physiologic monitoring devices (e.g., pedometers and heart rate monitors), and internet mediated counseling. Initial studies in adults demonstrate that interactive technologies can intensify antismoking attitudes, improve prevention behaviors, influence dietary habits, increase physical activity, strengthen adherence to medical treatment plans, or improve chronic disease self-management (Norman 2007). The few published pediatric studies of exer-gaming include design limitations such as: 1) small sample sizes; 2) inadequate measures of physical activity and body composition (Trost 2008), and 3) an absence of the use of evidence-based behavioral strategies, important components of interventions designed to increase and sustain physical activity ([name] 2006). Published exercise studies have not included children at increased CVD risk. “Exer-gaming” techniques should be tested in pediatric patients with CVD risk factors to determine if they increase physical activity, and whether this increases physical fitness, decreases body fat, and reduces CVD risk factors.

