### III. Recruitment

#### a. Inclusion and Exclusion Criteria

##### Main Experiment

###### Inclusion criteria

- enrolled in grades 3-5
- able to attend GoKids and school-based weekly educational sessions for 12 weeks and complete baseline and follow-up testing
- informed consent from a parent or legal guardian and written assent from the child
- English speaking child
- free from medical conditions that would prohibit exercise as indicated by permission to participate in school physical education, and by review of screening questions with clearance from primary care provider as necessary

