#### **e. Baseline Assessment**

##### **Main Experiment**

All participants will be asked to attend GoKids UMass Boston (Boston, MA) for baseline measurements. During the baseline visit, research personnel will screen for eligibility and obtain a comprehensive assessment of baseline cardiovascular, physical activity, and psychosocial measures under the supervision of trained research personnel and exercise physiologists. Non-fasting finger stick total cholesterol (TC) and high-density lipoprotein (HDL) testing will be offered. If no exclusionary criteria become apparent during baseline measurements, participants will be individually randomized to either the center-based exercise intervention (*GoKids*) or an *Advice-Only* condition for 12 weeks, with a follow-up evaluation at 12 weeks after baseline. See Study Measurements and Data Collection for more information.

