### b. Intervention Protocol

Following the baseline measurements, participants will be individually randomized into one of the following two treatment conditions: *GoKids* and *Advice-Only*. All participants will receive weekly group nutrition and activity education sessions lasting approximately 30 minutes supported by printed dietary, exercise and motivational advice adapted from existing materials (clinic materials, AHA, CDC and NHLBI materials). The sessions will be taught by UMass student educators trained to deliver a standard message. The *Advice-Only* intervention will consist entirely of these weekly sessions. It was felt to be unethical to offer no support for following a heart-healthy lifestyle to children randomized to the *Advice-Only* condition given the high rate of overweight/obesity and generally poor diet and activity levels in our study population. The *Advice-Only* group will be offered the 12-week GoKids physical activity experience at the close of the trial as an incentive for participation. Children in both groups will receive a small incentive during week 6 and then at the close of the intervention. In addition, classroom and school-wide incentives will be offered, such as healthy lifestyle education sessions for other classes; details will be discussed with the school principal.

The *GoKids* group will receive the GoKids integrated program which uses theory-based behavioral strategies and center-based exercise training. It includes an initial exercise consultation, orientation, and tri-weekly training at *GoKids* Boston. Previous research from GoKids Boston indicates that the energy expenditure from playing interactive video games is comparable to what is expended while walking on a treadmill for the same amount of time. In addition, the use of interactive video games is at a sufficient intensity to engage the participant in MVPA (Bailey et al., 2008). Exercise sessions in the *GoKids* condition will occur 3 times per week lasting 60 minutes each session, for 12-weeks and will include a variety of exercise training activities using the latest interactive exercise games, treadmills, elliptical machines, and strength training equipment located at the UMass facility. All sessions will be supervised by a trained exercise physiologist, with nurse practitioner support available and the classroom teacher present and active with the students.

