### c. Randomization Procedures

Staff at the Clinical Research Program (CRP) of CHB will run the randomization software based on the specifications provided by the Principal Investigator (PI). The randomization software (SciRAN) was developed by the Clinical Research Information Technology (CRIT) in collaboration with CRP Biostatistics Core. SciRAN is password protected and access is restricted to designated CRIT and CRP personnel only. The system is designed to a) generate unique and unpredictable random assignments to treatment groups; b) provide users with an audit trail of the process including a verifiable link between subject ID and treatment assignment; and c) provide standard documentation tools.

Key randomization specifications for this pilot study include the following:

- One hundred (100) subjects randomized at CHB, 50 to each of the two treatment arms.
- Children in third through fifth grade will be randomly assigned to one of the following two treatment arms after eligibility is confirmed:
  - Group A:** Nutrition education + exer-gaming sessions
  - Group B:** Nutrition education
- Stratification: normal weight and overweight/obese participants
- The PI will be blind to treatment assignment and block sizes.

Prior to running the randomization program for the study, Dr. [name] confirmed the randomization specifications by completing the Randomization Checklist. [name], Senior CRP Biostatistician, approved the specifications and prescribed the randomization block sizes. Finally, the CRP Data Manager ran the randomization program inputting the approved specification and produced the following randomization documents:

- The Master Randomization Lists: One list per school site: the Master Randomization list includes randomization identifiers, corresponding treatment assignments and randomization blocks.
- The Investigator's Randomization List, which is a 'blinded' version of the Master Randomization List, i.e., absent the treatment assignments and randomization blocks. The investigator's Randomization List will be delivered to the PI.

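### Change in obesity is to be measured by BMI percentile, a bounded scale that increasingly compresses change at the top, so a benefit in obese children would be attenuated

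*Protocol*

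**What the plan says.** Protocol section I.a (Secondary Aims) states a comparative hypothesis: anthropometric measures should improve more with GoKids than with Advice-Only. The endpoints are "Percent body fat by BIA, degree of obesity by BMI percentile, waist circumference, blood pressure". BMI percentile is the only BMI-based measure among them, and no BMI in kg/m², BMI z-score or similar metric is named as an endpoint elsewhere.

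Three other places bear on the choice of scale.

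- **Who is enrolled.** The Main Experiment criteria in III.a ask that the child be "enrolled in grades 3-5" and set no weight limit. Section IV.c lists "Stratification: normal weight and overweight/obese participants", so both ends of the BMI range are expected. Section IV.b justifies the control condition "given the high rate of overweight/obesity and generally poor diet and activity levels in our study population", without a figure.
- **Size and duration.** Section IV.c gives "One hundred (100) subjects randomized at CHB, 50 to each of the two treatment arms"; section III.e describes randomisation to 12 weeks of either condition "with a follow-up evaluation at 12 weeks after baseline".
- **Data available.** Height and weight are measured (V.b). Date of birth and gender are on the enrolment form (V.a).

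**The concern.** Percentiles suit classification: they place a child below or above a cut-off. They are a poor measure of change in how obese a child is, because every child at or above the 95th percentile lies within the last five points of the scale. A child well above that cut-off can have a real fall in relative BMI and hardly move.

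In a sample running from normal weight to obese, the same relative change in BMI is a large percentile change in a child near the median and a small one in an obese child. A between-arm comparison of percentile change therefore gives most weight to children for whom lowering BMI is not the aim. At stake is a BMI result that understates a benefit in obese children and could be read as no effect on obesity.

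**Working it through.** The protocol gives no effect size, SD, alpha or power for this endpoint, so there is no stated figure to reproduce. The check has two parts.

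**1. The scale itself (no outside data needed)**

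Percentile = 100 × Φ(z), where z is the BMI z-score. A fall of 0.2 SD from z moves the percentile by 100 × [Φ(z) − Φ(z − 0.2)].

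| Starting point | z | Fall in percentile points | Median fall ÷ this fall |
|---|---|---|---|
| 50th | 0 | 7.93 | 1 |
| 85th | 1.04 | 5.13 | 7.93/5.13 = 1.5 |
| 95th | 1.645 | 2.42 | 7.93/2.42 = 3.3 |
| 99th | 2.33 | 0.67 | 7.93/0.67 = 12 |
| above the 99th | 2.5 | 0.45 | 7.93/0.45 = 18 |

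The compression is mild at the 85th percentile, clear at the 95th and severe from the 99th up.

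**2. What this could cost in power (illustration)**

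*From the protocol:* 50 children per arm; normal-weight and overweight/obese children both enrolled.

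*Assumed, not in the protocol:* baseline z ~ N(0.8, 1.1); SD of the 12-week change in z 0.20 (range 0.20 to 0.30); true benefit 0.15 z (range 0.10 to 0.15); overweight/obese means z ≥ 1.036 (85th percentile), obese means z ≥ 1.645 (95th); two-sided 5% t-test on change. The same simulated children were analysed on both scales, with 3,000 replicates per setting.

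| Setting | z-score: power at 0.15 z, SD 0.20 | Percentile: same setting | z-score: over the range | Percentile: over the range |
|---|---|---|---|---|
| All children, 50 per arm, uniform benefit | 0.96 | 0.90 | 0.39–0.96 | 0.29–0.90 |
| Obese children only, 25 per arm | 0.73 | 0.52 | 0.22–0.73 | 0.16–0.52 |
| All children, 50 per arm, benefit only in overweight/obese | 0.32 | 0.10 | 0.10–0.32 | 0.06–0.10 |

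As a check on the simulation, the two-sample power formula for 50 per arm, difference 0.15 and SD 0.20 gives 0.963 on the z scale, against 0.960 simulated. Percentile has the lower power in every setting tried.

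Two points on reading the table:

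- The assumed baseline puts 1 − Φ((1.036 − 0.8)/1.1) = 0.42 of children in the overweight/obese group. In the last row the average benefit over all children is therefore only 0.15 × 0.42 = 0.06 z, which is why the z-score also has low power there.
- The same baseline puts 1 − Φ((1.645 − 0.8)/1.1) = 0.22 of children above the 95th percentile, about 22 of 100. The row with 25 obese children per arm compares the two scales within obese children; it does not forecast how many this trial would have.

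**The case against.** Four arguments can be made for leaving the endpoint alone.

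*The analysis is not stated.* The protocol names a measure, not a test or model. Percentile and z-score correspond one to one for a given child, so a statistical analysis plan could analyse z, use ranks or report by weight stratum. This stands as far as it goes: the argument about arm means assumes that percentile change is compared as it is. But the scale is fixed in the protocol itself, for a claim of greater improvement, so the choice has not been left open.

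*The aim does not rest on BMI alone.* Percent body fat and waist circumference are listed beside it and do not share this ceiling. The primary aim is accelerometer-measured activity, and IV.c calls the study a pilot. All of this stands and limits the consequence.

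*The power figures rest on outside inputs.* They do. Baseline distribution, SD of change, benefit and subgroup size are all assumed. The compression in the first table depends on none of them.

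*Other metrics have limits too.* BMI z-score also compresses in the most obese children. This bears on which metric should lead; it does not make percentile a good measure of change.

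A reader might infer more: that the scale barely moves in overweight children, that the endpoint cannot show a benefit, or that its distribution is strongly skewed. The documents do not support these readings. At the 85th percentile, 5.13/7.93 = 65% of the median movement remains, and at the 95th 2.42/7.93 = 31%. With a uniform benefit the illustrated loss of power is modest. The protocol contains no data on the distribution.

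**Conclusion.** The concern holds as one of attenuation. BMI percentile is a poor scale for change in obesity in a sample that spans normal weight to obese. Near the 85th percentile the loss is slight; above the 95th it is strong, reaching 12-fold or more from the 99th up. If the benefit is uniform, the illustrated power falls only from 0.96 to 0.90. If it is confined to overweight and obese children, power on percentile is close to the 5% error rate; the z-score does better there but, at 0.32, is still weak, so changing the scale would not by itself make that scenario detectable.

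The compression follows from the definition of a percentile; the power figures hold only under the stated assumptions. One of several secondary endpoints is affected, and the primary conclusion does not depend on it. The change is worth making because it is cheap and because the current scale is least sensitive in the children whose obesity is greatest.

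**What to change.** In the Secondary Aims (section I.a), replace BMI percentile as the change endpoint with BMI (kg/m²) at 12 weeks, compared between arms with adjustment for baseline BMI, age and sex. Give BMI z-score as a supporting analysis, and note that it also compresses in the most obese children. Keep BMI percentile for classifying children by weight status and for describing the sample at baseline.

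The cost is one line in the endpoint list. Height, weight, date of birth and gender are already collected, so there is no new measurement and no added burden on the children. The drawback is that the result is slightly less familiar to families than a percentile.

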#### **Sub-Study Aims (exploratory):**

The *GoKids* intervention group will show greater improvement in CVD risk measurements, including vascular reactivity, fasting lipid and glucose metabolism parameters, resting energy expenditure, left ventricular hypertrophy, and inflammatory measures compared to the *Advice-Only* condition.

**Primary Endpoint:** change in insulin resistance as measured by HOMA-IR.

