### b. Background and Rationale

Obesity is increasingly common in childhood and adolescence, and is a major threat to health. Childhood obesity is predictive of risk for chronic conditions, including type 2 diabetes and cardiovascular disease (CVD) in adulthood (Morrison 2008), and obese pediatric patients have high rates of cardiovascular risk factors during childhood. Declining levels of physical fitness among children and adolescents contribute to the obesity-associated health risks of future generations (American Heart Association 2005). Physical activity is known to have physiologic benefits in many areas; recommendations to increase physical activity levels in children are evidence-based (Strong 2005).

Exercise training is a type of physical activity that can improve physical fitness. Exercise training improves a host of physiological risk factors and provides psychosocial benefits for children who are at increased CVD risk, including those with obesity (Klijn 2007) and diabetes (Caranti 2007). Furthermore, several recent pediatric studies suggest that exercise training reduces cardiometabolic risk factors (Ferguson 1999) and the intra-individual clustering of cardiometabolic risk factors (Reinehr 2009). Reduction in risk factors may occur both by direct effects (e.g. blood pressure reduction, increasing HDL), and indirectly through weight reduction. Despite evidence of its benefits, exercise training prescribed by physicians for overweight children is traditionally vague, developmentally inappropriate, and/or fraught with psychological financial & practical barriers. Recommendations may not be supported by sufficient motivational assistance.

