##### Sub-Study

###### Inclusion criteria

- participation in the Main Experiment
- able to attend CHB CTSU for two ~2 hour visits occurring at baseline and follow-up
- informed consent for the Sub-Study from a parent or legal guardian and written assent (from the child)
- HDL <50 mg/dL, TC > 170 mg/dL, blood pressures > 90th percentile for age, gender and height, OR waist circumference > 90th percentile (NHANES)

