## **VI. Adverse Event Reporting**

### **a. Risks and Discomforts**

#### **Main Experiment**

Risks and discomforts are expected to be minimal in children enrolled in the Main Experiment, as the intervention will involve physical activity aimed at children. The fingerstick TC and HDL testing will be optional. Minimal risk due to injury may be associated with the exercise intervention, but no more than a school-based physical education class. Questionnaires occasionally can be distressing. Support will be available from GoKids staff experienced in interacting with children.

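### Total cholesterol includes HDL, so the HDL rise the protocol expects offsets any fall in TC; non-HDL cholesterol with stated directions would be a cleaner secondary endpoint at no cost

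*Protocol*

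**What the plan says.** The lipid hypothesis in the protocol's Secondary Aims reads "Non-fasting total cholesterol (TC) and HDL will improve from baseline in the group receiving the" GoKids intervention, more than in the Advice-Only group. The endpoint is "Change in Cholestech TC and HDL from baseline". Neither sentence says which direction counts as improvement.

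The directions can be inferred from two other places. The Background and Rationale says "Reduction in risk factors may occur both by direct effects (e.g. blood pressure reduction, increasing HDL), and indirectly through weight reduction", so HDL is expected to go up. The Sub-Study inclusion criteria use "HDL <50 mg/dL, TC > 170 mg/dL" among the risk markers, so a lower TC and a higher HDL are the favourable directions.

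Both values come from one test. Under Baseline Assessment, "Non-fasting finger stick total cholesterol (TC) and high-density lipoprotein (HDL) testing will be offered"; under Risks and Discomforts, "The fingerstick TC and HDL testing will be optional". The main experiment names no non-HDL or ratio endpoint. The Sub-Study looks at "fasting lipid and glucose metabolism parameters", but as an exploratory aim in a selected subset.

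**The concern.** TC contains HDL. An intervention that raises HDL, as the Background expects, pushes TC up by the same amount, while the hypothesis requires TC to come down. The two measures are therefore not separate readings of benefit: part of any success on HDL is subtracted from the result on TC.

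This makes a change in TC hard to read in either direction. A small fall, or none, may hide a worthwhile fall in the non-HDL fraction. A fall may also come partly or wholly from a loss of HDL. Since the protocol does not say what improvement in TC means, the reader has no fixed rule for interpreting the result. What is at stake is the clarity and sensitivity of one half of one secondary aim.

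**Working it through.** **Inputs from the protocol.** 100 children, 50 per arm ("One hundred (100) subjects randomized at CHB, 50 to each of the two treatment arms", Randomization Procedures). Lipid testing is optional, so 50 per arm is an upper bound for this endpoint. The protocol states no lipid effect size, SD, alpha or power, so there is no figure of its own to reproduce.

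**Assumptions, shown as ranges.** Between-arm difference in change: HDL rise up to 5 mg/dL, non-HDL fall up to 10 mg/dL. SD of change 15 to 20 mg/dL, taken as the same for TC and non-HDL. Two-sided alpha 0.05.

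**Identity.** TC = HDL + non-HDL, so change in TC = change in HDL + change in non-HDL.

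**Power.** SE = SD × √(2/50) = 0.2 × SD, which is 3 mg/dL at SD 15 and 4 mg/dL at SD 20. Power in the beneficial direction = Φ(|effect|/SE − 1.96). For example, an effect of 2 at SD 20 gives Φ(0.50 − 1.96) = 7%, and an effect of 5 gives Φ(1.25 − 1.96) = 24%.

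| HDL | non-HDL | TC | Power for TC (SD 15; 20) | Power for non-HDL (SD 15; 20) |
|---|---|---|---|---|
| +2 | −10 | −8 | 76%; 52% | 92%; 71% |
| +3 | −10 | −7 | 65%; 42% | 92%; 71% |
| +5 | −10 | −5 | 38%; 24% | 92%; 71% |
| +3 | −5 | −2 | 10%; 7% | 38%; 24% |
| +5 | −5 | 0 | 2.5%; 2.5% | 38%; 24% |
| +5 | −3 | +2 | TC moves the wrong way | 17%; 11% |
| +3 | 0 | +3 | TC moves the wrong way | no effect to detect |

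The first four rows show dilution, the fifth cancellation and the last two reversal. In the opposite case, HDL −4 with non-HDL unchanged gives TC −4: TC looks better although only HDL has worsened.

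**Scale.** The difference detectable with 80% power is (1.96 + 0.84) × SE, about 8.4 mg/dL at SD 15 and 11.2 mg/dL at SD 20. An HDL offset of 2 to 5 mg/dL is a material part of that.

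**Check on the equal-SD assumption.** The variance of change in non-HDL = SD(TC)² + SD(HDL)² − 2r × SD(TC) × SD(HDL), where r is the correlation of the two changes. Take an assumed SD of 8 mg/dL for change in HDL and the unfavourable case r = 0. The non-HDL SD is then √(225 + 64) = 17.0 or √(400 + 64) = 21.5. For HDL +3 and non-HDL −5, power for non-HDL is Φ(5/3.40 − 1.96) = 31% or Φ(5/4.31 − 1.96) = 21%, still well above the 10% or 7% for TC.

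**The case against.** The strongest reply is that TC is never read alone. HDL change is reported beside it, so an HDL gain or loss shows up in its own endpoint. A reader might infer that the intervention's whole lipid benefit would disappear, or that a fall in HDL would pass as success. The protocol does not support that inference, because the HDL result would show either one. A reader might also infer that the aim would be declared failed if TC stayed flat. The protocol sets no success rule for the lipid aim, so this does not follow.

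Nor is there a contradiction. TC down with HDL up is a coherent hypothesis: it says that non-HDL falls by more than HDL rises. It would be too strong to say that the HDL rise does cancel or reverse the TC effect, because that depends on relative sizes the protocol does not give.

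Two further points have weight. The between-arm difference in non-HDL change can be recovered, among children with both values, as the TC difference minus the HDL difference. And at a non-HDL fall of 3 to 5 mg/dL, power is low even for non-HDL (11% to 38% in the table).

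All of this limits the point, but it does not repair the TC half of the endpoint. Subtracting two reported mean differences gives no standard error without the correlation between the two changes, and it is not a pre-specified analysis. An analysis plan could add a derived variable, but the choice of TC and the claim that it will improve are fixed in the protocol's Secondary Aims.

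**Conclusion.** The point holds as an improvement to a secondary endpoint, not as an error in the plan. What is certain, by definition, is that any HDL gain offsets a fall in TC mg for mg. The protocol both expects that gain and leaves the direction of improvement unstated. How much this costs is conditional. The TC effect is diluted if non-HDL falls by more than HDL rises, cancelled if the two are equal, and reversed if HDL rises by more.

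All effect sizes and SDs used here are assumptions, and the sample per arm is an upper bound. The HDL endpoint keeps its full information, and the primary MVPA endpoint is untouched.

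**What to change.** In the Secondary Aims, replace the lipid endpoint with two measures and give each a direction: change from baseline in non-HDL cholesterol (Cholestech TC minus HDL from the same fingerstick; a fall is improvement) and change from baseline in HDL (a rise is improvement). Reword the hypothesis sentence to match, and keep TC as a descriptive measure.

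The cost is a few words in the protocol and one subtraction per child and visit. Both values come from the same test, and Form 1 (Anthropometric and Lab Data) is already completed at baseline and 12 weeks. No new sample, test or visit is needed.
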